## **Subjects**

Target population Pregnant women with prenatal care in the health care centres of the ASSIR from Catalonia

Inclusion criteria. Older pregnant women with prenatal care in the centres study, with childbirth in the reference hospitals, who wish to participate in the study and want to fill in the birth plan

Exclusion criteria. Illiteracy, language barrier, drug addiction, alcoholism, grade 2, 3 and 4 heart disease, severe associated maternal pathology, type I-II diabetes, uterine malformation, diagnosed foetal malformation, threatened preterm birth, twin or multiple pregnancy, cervical incompetence, previous perinatal death, intrauterine growth retardation, placenta previa, isoimmunization, mild-severe preeclampsia, premature rupture of membranes, maternal infection.

Sample size. The sample calculation has been made based on the main variable of the study “presentation of birth plans”. Based on the descriptive pilot study (n = 211 pregnant women), 48% of the women who receive the usual advice presented the

birth plan to the hospital. It is estimated that this prevalence may be higher in women who receive counselling, around 68%. In this study, a randomized, multicentre and parallel experimental design in clusters is proposed (4 ASSIRs participate). Applying an alpha error of 5%, a beta error of 20% and taking into account the influence of the clusters in the analysis, a total of 133 are required in the control group and 133 in the intervention group. 15% loss to follow-up has been estimated. The calculation has been carried out using the macros of SPSS V22. An interim analysis will be performed to assess whether the sample size needs to be recalculated so that there is sufficient power for the subgroup analysis.

Sampling technique. In the random assignment of ASSIR, the characteristics of the reference hospitals will be taken into account, since they have different levels of care. Thus, two ASSIRs will be assigned to the intervention group and two to the control. For this assignment, the Epidat 4.1 program will be used. This type of assignment has been chosen to avoid contamination among midwives who will or will not receive specific training on birth plan counselling based on shared decision making.

The sampling technique of pregnant women within each ASSIR will be consecutive and proportional to the number of first visits (see table 1).

Table 1. Proportional sampling according to the number of first ASSIR visits

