#### Characteristics of the intervention in the intervention group

Phase I. Training intervention for midwives. There will be a 4-hour workshop on counselling in the birth plan, based on the communicative intervention of negotiation of options in shared decision making by Epstein et al, which consists of: understanding the experience and expectations of the pregnant woman, construction of a collaborative relationship between the pregnant woman and the professional, provide information according to the existing level of evidence and current recommendations, and verification of understanding and compliance 

Phase II. Intervention in pregnant women. The pregnant women will receive the birth plan from the midwives in the prenatal control visit between 24-28 weeks of gestation that they will complete at home. Later, in the prenatal control visit between 29-33 weeks of gestation, the pregnant women will receive the counselling intervention from the midwife, which will consist of standardized advice on the birth plan based on shared decision making according to Epstein et al  and in the delivery of an informative leaflet  based on the existing scientific evidence of the aspects expressed in the birth plan. The counselling of the midwife of the pregnant women will include the following activities: it will explore the previous experiences and expectations of the pregnant woman regarding the childbirth; establish with the pregnant woman a collaborative relationship in decision-making; explain the existing evidence for each aspect of the birth plan; will inform of the updated recommendations on the aspects specified in the birth plan and will check the understanding of the information provided to the pregnant woman. The midwife will then deliver a second birth plan that the pregnant woman will fill out at her home and that she must deliver a copy to the midwife at the prenatal visit between 34-40 weeks of gestation. The midwife will instruct the pregnant woman to present the original to the reference hospital.

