### **Data collection procedure**

The midwives of the ASSIR will carry out the recruitment of the pregnant women in the control and intervention group in the prenatal visit of 24-28 weeks of gestation and they will be explained what the study consists of verbally and in writing. If they wish to participate, the informed consent will be collected and then the midwife will collect the sociodemographic and obstetric data and will deliver the birth plan for the pregnant women to fill in at home.

In the prenatal visit of 29-33 weeks of gestation, midwives will collect the completed birth plans and will deliver a new birth plan that the women will fill out at home and will be instructed to deliver a copy at the prenatal visit between the 34-40 weeks of gestation.

The midwife will keep a copy and will indicate to the pregnant women that the original must be presented to the hospital. In the women in the intervention group, the midwives will carry out the standardized counselling intervention in the preparation of the birth plan based on the shared decision making of Epstein et al and in the pregnant women in the control group, the midwives will carry out the usual practice of counselling the plan of birth.

In the postpartum visit between hospital discharge and the 6th postpartum week, the midwives of the control and intervention group will collect the childbirth data and deliver an sealed envelope with the questionnaire of questions about the childbirth and the birth plan, sufficient information satisfaction received during pregnancy about the delivery, usefulness of completing the birth plan, intention to use it in the next pregnancy and the MacKey questionnaire on the satisfaction of childbirth.

**Pilot test.** A pilot test will be carried out with 10 pregnant women in each ASSIR.

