### **Analysis.**

A descriptive analysis of all variables will be carried out. The categorial ones with frequencies and percentages; the quantitative ones with mean and standard deviation and if they do not comply with a normal distribution, the median, minimum, and maximum will be observed. The statistical software package SPSS 22.0 will be used. Homogeneity tests between the groups will be performed for the main sociodemographic variables to analyse the comparability of the groups. Hypothesis contrast tests, Chi-square test and Student's t test will be performed. A statistical significance level of 5% will be used. Confidence level will be settled on 95%. A multivariate analysis, relative risks and number of subjects will be calculated with a confidence interval of 95%.

**Bibliographic search.** The databases consulted for the search were MEDLINE; Cochrane; EBSCO; CINAHL and CUIDEN from 2000 to 2016 Keywords: birth plans, assessment, midwife, satisfaction, decision making.

**Ethical aspects.** The principles of the Declaration of Helsinki  will be considered and the necessary precautions will be taken to minimize the possible repercussions on pregnant women during the investigation according to the recommendations of the Belmont report.  Authorization will be requested from the Committee on Clinical research ethics of the Jordi Gol i Gorina Foundation for the ASSIR of the Catalan Institute of Health. The information sheet and informed consent is common for participants in the control and intervention group. Throughout the process, the confidentiality of the data will be guaranteed according to Organic Law 15/1999, on the protection of confidential data .

**Difficulties and limitations.** Women can also access birth plan information through other pregnant women or other means such as the internet that could modify decisions regarding it. To avoid contamination among midwives in the counselling

activity, a randomization of ASSIR has been chosen. The possible losses that may be due to a change in the risk of gestation after 29 weeks that limit following the completed birth plan and/or require a childbirth in a hospital other than that of reference. In situations where neonatal death occurs, the degree of satisfaction will not be evaluated.

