| Final design of the leaflet                                                                                                              |                |                       |                      |                  |          |                |                |              |                              |
| Training workshop for midwives of the intervention group                                                                                 |                |                       |                      |                  |          |                |                |              |                              |
| Test pilot                                                                                                                               |                |                       |                      |                  |          |                |                |              |                              |
| Data Collect                                                                                                                             |                |                       |                      |                  |          |                |                |              |                              |

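### Midwives who know their arm recruit women after cluster allocation on a willingness criterion, and the stated safeguards cannot show or ensure that the two groups are comparable

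*Protocol*

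**What the plan says.** **Allocation.** Under Subjects (sampling technique), "two ASSIRs will be assigned to the intervention group and two to the control". The stated reason is to "avoid contamination among midwives who will or will not receive specific training on birth plan counselling based on shared decision making".

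**Training.** The intervention arm begins with "Phase I. Training intervention for midwives. There will be a 4-hour workshop on counselling in the birth plan"; contact with women is Phase II. The Timeline also lists the workshop before the pilot test and data collection.

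**Recruitment.** Under Data collection procedure, "The midwives of the ASSIR will carry out the recruitment of the pregnant women in the control and intervention group". This happens at the 24-28 week visit, where the study is explained orally and in writing, consent is taken and the sociodemographic and obstetric data are recorded.

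**Eligibility.** Women must be among those "who wish to participate in the study and want to fill in the birth plan". The main variable for the sample size is whether the birth plan was presented to the hospital.

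**Safeguards.** The protocol states four things that bear on comparability:
- consecutive sampling within each ASSIR, proportional to first visits (Subjects);
- one information sheet and consent form for both arms (Ethical aspects);
- baseline testing: "Homogeneity tests between the groups will be performed for the main sociodemographic variables to analyse the comparability of the groups" (Analysis);
- a multivariate analysis with relative risks (Analysis), without saying which comparison it serves. The named hypothesis tests are chi-square and Student's t.

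The section on difficulties and limitations covers outside information, contamination between midwives and losses. It does not mention differential recruitment.

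**The concern.** Randomising units protects the comparison of units. It does not balance women who are chosen, or who choose themselves, after the units' arms are known. The person who explains the study and takes consent knows what the woman will receive, and in one arm has just been trained to deliver it. Whether a woman wants to complete a birth plan is a soft judgement, and it is a near relative of whether she later hands one in. If that judgement, or the oral explanation before it, differs by arm, the proportion presenting a plan can differ with no effect of counselling.

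The one step whose declared purpose is comparability is a set of significance tests on sociodemographic variables. A non-significant result there could be taken as reassurance that it cannot give. With two units per arm, averaging over many clusters will not dilute a difference in recruitment style either.

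**Working it through.** The protocol gives no figure for recruitment bias, so there is none to reproduce. Its 133 per arm is used only as an input. That figure can be neither confirmed nor refuted here, because no intracluster correlation or design effect is stated.

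**Step 1. Do recruiters know the arm?** The protocol does not say so in words. It follows from three facts: allocation is by ASSIR, only intervention units are trained, and training comes before contact with women. The recruiters are those same midwives, and no blinded or independent recruiter is described.

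**Step 2. What can a homogeneity test detect?** Inputs: 133 per arm (Subjects); 5% level (Analysis), assumed two-sided; a binary covariate centred on 50% (assumed); clustering ignored. Baseline data are taken at enrolment, so the number is 133, before losses.

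SE = √(2 × 0.5 × 0.5 / 133) = 0.0613. For a 10-point imbalance, 0.10 / 0.0613 = 1.63, and power ≈ Φ(1.63 − 1.96) = Φ(−0.33) ≈ 37%.

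| Imbalance | Power |
|---|---|
| 5 points | about 13% |
| 10 points | about 37% |
| 15 points | about 69% |

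A 10-point imbalance is therefore missed about 63% of the time, nearly two times in three. A test that properly allowed for two units per arm would have less power still. Motivation is not among the listed baseline variables, so no such test addresses it.

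**Step 3. How large could a bias be?** The protocol has no data on this, so every input is assumed. Let d be the difference between arms in the share of strongly motivated women, and g the gap in presentation rate between motivated and other women. Then bias = d × g.

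| | g = 20 points | g = 40 points | g = 60 points |
|---|---|---|---|
| d = 10 points | 2 | 4 | 6 |
| d = 20 points | 4 | 8 | 12 |
| d = 30 points | 6 | 12 | 18 |

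The target difference is 68% − 48% = 20 points. With no true effect, a 48% control rate, 133 per arm, clustering ignored and the bias favouring the intervention, the chance of a significant result in that direction (nominally 2.5%) is about 5% at 2 points, 26% at 8 points and 85% at 18 points. With the opposite sign, the same biases would hide a real effect.

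**Step 4. What does each safeguard do?**
- *Consecutive sampling* limits choice by the midwife. Willingness and consent still operate after allocation, and no count of women eligible, invited or declining is described, so adherence could not be checked afterwards.
- *Common consent form* fixes the written text, but not the oral explanation.
- *Homogeneity tests* neither prevent nor correct selection (Step 2).
- *Multivariate analysis* could correct for measured covariates if it were the primary comparison. The protocol does not make it so, and it cannot correct for motivation that was not measured.

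**The case against.** The strongest reply is that the protocol already contains the main countermeasure. Consecutive sampling to a fixed quota leaves midwives no stated discretion, the consent material is identical, and a multivariate analysis is planned. The willingness criterion applies equally in both arms and screens out unwilling women, which may narrow differences in motivation. The homogeneity tests are not described as a correction or as a gate on the analysis. Naming covariates is commonly left to a statistical analysis plan, which is not at hand.

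Much of this stands, and it rules out several stronger readings that a reader might infer:
- *That baseline testing is the only safeguard and selection is left wholly uncorrected.* The other three measures are in the text.
- *That all recruiters are trained.* Training applies to the intervention arm only.
- *That needing 266 women out of 6,496 first visits (4.1%) shows wide room to choose.* The denominator precedes a long list of exclusions, and under consecutive sampling a small fraction may mean only that the quota fills quickly.
- *That the bias must favour the intervention.* Trained midwives might equally enrol more hesitant women.
- *That the absence of a covariate list is itself a fault.* It may be in the analysis plan.

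What the reply does not meet is narrower. The recruitment sequence, the criterion and the use of significance tests to judge comparability are fixed in this protocol. A later analysis plan can name covariates, but it cannot rebuild a record of women approached that was never kept.

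**Conclusion.** The point holds as a risk that the plan does not adequately control. It is not a demonstrated bias. Recruitment after allocation by midwives aware of their arm is a sound inference from the design, and the willingness criterion sits close to the main outcome. Consecutive sampling and common consent lessen the risk but cannot be verified as planned. Homogeneity tests are weak evidence of comparability: about 37% power for a 10-point imbalance, assuming a 50% covariate, a two-sided 5% level and no clustering.

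Neither the size nor the direction of any bias is established. The range of about 2 to 18 points rests entirely on assumed values. It shows only that plausible inputs run from negligible to nearly the whole 20-point target. The remedy is cheap and the outcome at risk is the main one, so the changes should be made.

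**What to change.** 1. **Analysis.** Do not use baseline significance tests as the criterion of comparability; describe baseline characteristics by arm and by ASSIR instead. Make the primary comparison of birth plan presentation one adjusted for a fixed set of covariates already collected at the 24-28 week visit: age, nationality, educational level, previous births, maternal education and internet use. The adjustment applies whatever the baseline data show.
2. **Recruitment record.** Keep a simple log in each ASSIR of women eligible, invited and consenting, and report the counts by ASSIR. This makes the consecutive sampling already planned verifiable.
3. **Limitations.** State that recruiters know the allocation and that unmeasured motivation may still differ between arms after adjustment.

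The cost is a short log kept by the midwives and slightly more analysis work; no new baseline variable is needed. Adjustment will not remove a difference in motivation that was not measured, so the log and the stated limitation are needed as well as the model.

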### **Analysis.**

A descriptive analysis of all variables will be carried out. The categorial ones with frequencies and percentages; the quantitative ones with mean and standard deviation and if they do not comply with a normal distribution, the median, minimum, and maximum will be observed. The statistical software package SPSS 22.0 will be used. Homogeneity tests between the groups will be performed for the main sociodemographic variables to analyse the comparability of the groups. Hypothesis contrast tests, Chi-square test and Student's t test will be performed. A statistical significance level of 5% will be used. Confidence level will be settled on 95%. A multivariate analysis, relative risks and number of subjects will be calculated with a confidence interval of 95%.

**Bibliographic search.** The databases consulted for the search were MEDLINE; Cochrane; EBSCO; CINAHL and CUIDEN from 2000 to 2016 Keywords: birth plans, assessment, midwife, satisfaction, decision making.

**Ethical aspects.** The principles of the Declaration of Helsinki  will be considered and the necessary precautions will be taken to minimize the possible repercussions on pregnant women during the investigation according to the recommendations of the Belmont report.  Authorization will be requested from the Committee on Clinical research ethics of the Jordi Gol i Gorina Foundation for the ASSIR of the Catalan Institute of Health. The information sheet and informed consent is common for participants in the control and intervention group. Throughout the process, the confidentiality of the data will be guaranteed according to Organic Law 15/1999, on the protection of confidential data .

**Difficulties and limitations.** Women can also access birth plan information through other pregnant women or other means such as the internet that could modify decisions regarding it. To avoid contamination among midwives in the counselling

activity, a randomization of ASSIR has been chosen. The possible losses that may be due to a change in the risk of gestation after 29 weeks that limit following the completed birth plan and/or require a childbirth in a hospital other than that of reference. In situations where neonatal death occurs, the degree of satisfaction will not be evaluated.

**Applicability and practical utility.** Advice on shared decision making in the birth plan can incorporate improvements in conscious decision-making and greater autonomy in pregnant women, improving the information received during pregnancy on aspects of their childbirth. It can incorporate quality indicators on the care received and satisfaction in primary care and hospital.

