| ASSIR             | First visits | Proportion | Sample size |
|-------------------|--------------|------------|-------------|
| Mollet del Vallés | 1017         | 15.1%      | 41          |
| Badalona          | 1933         | 29.6%      | 79          |
| Granollers        | 2260         | 35.7%      | 94          |
| Dreta Eixample    | 1286         | 19.6%      | 52          |
| Total             | 6496         | 100%       | 266         |

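### Hospital level of care guides the allocation of ASSIRs but is absent from the named tests; with unequal ASSIR quotas, pooling women can undo the balance sought

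*Protocol*

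**What the plan says.** In the Protocol's Subjects section, the sampling paragraph makes the reference hospital part of the allocation: "In the random assignment of ASSIR, the characteristics of the reference hospitals will be taken into account, since they have different levels of care". It adds that "two ASSIRs will be assigned to the intervention group and two to the control". Recruitment within each ASSIR "will be consecutive and proportional to the number of first visits", and Table 1 turns this into quotas of 41 (Mollet del Vallés), 79 (Badalona), 94 (Granollers) and 52 (Dreta Eixample).

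The Analysis section names the tests: "Hypothesis contrast tests, Chi-square test and Student's t test will be performed". It also announces a multivariate analysis and relative risks, without naming covariates. The comparability check is limited: "Homogeneity tests between the groups will be performed for the main sociodemographic variables to analyse the comparability of the groups". Neither the hospital nor its level appears in the lists of independent, sociodemographic, obstetric or outcome variables.

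**The concern.** The sponsor judged hospital level important enough to guide the assignment of ASSIRs. The named tests then compare pooled women as if that factor did not exist. Spreading level over ASSIRs balances it between ASSIRs. It balances it between women only if the ASSIRs contribute similar numbers, and Table 1 says they do not.

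Level could plausibly matter for the main variable. Presentation happens at the hospital, and one listed reason for not presenting is that the attending professionals did not ask. The plan's content is also agreed hospital by hospital (Data collection and tools). If presentation does differ by level, part of that difference can enter the crude comparison and be read as an intervention effect, or mask one. There is only one draw of four ASSIRs, so within this trial it cannot average out.

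**Working it through.** **Inputs from the Protocol.** The quotas are 41 + 79 + 94 + 52 = 266, with two ASSIRs per arm. The planned rates are 48% and 68%, so the planned difference is 20 points. Recomputing the quotas from first visits (visits / 6,496 × 266) gives 41.6, 79.2, 92.5 and 52.7, close to the printed values, which are used below. The stated 133 per arm rests on a cluster allowance for which no value is given, so it cannot be reproduced; this point does not depend on it.

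**Assumptions.** The Protocol gives neither the level of each hospital nor presentation by level. I assume two levels, each held by two ASSIRs and split one per arm, and a gap *g* in presentation between levels of 10, 20 or 30 points.

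**Step 1: imbalance in level mix.** Let *d* be the share of women from one level in arm 1 minus that share in arm 2. There are three pairings and two splits of each.

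| ASSIRs sharing Mollet's level | Arm 1 | Arm 2 | Shares | *d* (points) |
|---|---|---|---|---|
| Mollet, Badalona | Mollet + Granollers | Badalona + Eixample | 41/135 v 79/131 | −29.9 |
| Mollet, Badalona | Mollet + Eixample | Badalona + Granollers | 41/93 v 79/173 | −1.6 |
| Mollet, Granollers | Mollet + Badalona | Granollers + Eixample | 41/120 v 94/146 | −30.2 |
| Mollet, Granollers | Mollet + Eixample | Granollers + Badalona | 41/93 v 94/173 | −10.2 |
| Mollet, Eixample | Mollet + Badalona | Eixample + Granollers | 41/120 v 52/146 | −1.4 |
| Mollet, Eixample | Mollet + Granollers | Eixample + Badalona | 41/135 v 52/131 | −9.3 |

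Swapping the arms reverses the sign, which gives 12 combinations. In 4 of them the imbalance is about 30 points; in the other 8 it is 1.4 to 10.2.

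**Step 2: shift of the crude risk difference** = *g* × *d*.
- Largest imbalance (30.2): 3.0, 6.0 and 9.1 points for *g* = 10, 20 and 30.
- Intermediate (10.2): 1.0, 2.0 and 3.1 points.
- Smallest (1.4): 0.1, 0.3 and 0.4 points.

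The mirror-image draws cancel, so the mean shift over the randomisation is zero.

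**Step 3: what equal weighting of ASSIRs does.** Let the levels have presentation *a* and *b*, and the effect be *e*. The intervention mean is (*a* + *b*)/2 + *e* and the control mean is (*a* + *b*)/2. The difference is *e*, whatever the quotas.

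**Step 4: what it costs in precision.** Ignoring clustering, the variance is proportional to (1/41 + 1/79 + 1/94 + 1/52)/4 = 0.01673. Pooling women gives 1/135 + 1/131 = 0.01504, 1/120 + 1/146 = 0.01518 or 1/93 + 1/173 = 0.01653. The ratio is 1.11, 1.10 or 1.01, so the standard error rises by about 1% to 5%.

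**Step 5: width of the unpaired interval.** With 2 df the critical t is 4.30. With 48% in every ASSIR and no clustering, the standard error is √(0.48 × 0.52 × 0.01673) = 6.5 points and the half-width about 28 points. A level gap *g* that remains in the unpaired standard error contributes √(*g*²/4 + *g*²/4) = *g*/√2, or 7.1 points at *g* = 10.

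**The case against.** Several stronger readings are tempting, and the document does not support them.

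- **That the relative risk is crude.** The Analysis section lists relative risks beside the multivariate analysis and does not say which produces them. A covariate list is commonly left to an analysis plan. What stands is narrower: the named tests have no hospital term, and no hospital variable is listed.
- **That allocation is stratified by level.** The Protocol says only that hospital characteristics are considered. It defines no strata, no pairing and no number of levels. With three or four levels, some level would sit in one ASSIR only and offer no within-level contrast between arms.
- **That the comparison is systematically biased.** Over the randomisation the shift averages to zero, so it is a chance imbalance between clusters. It overlaps with the clustering problem: with two equal levels around 48%, gaps of 10, 20 and 30 points correspond to intracluster correlations of (*g*/2)²/(0.48 × 0.52), about 0.01, 0.04 and 0.09.
- **That the chi-square type I error is about 8%, 16% or 31%.** Those values belong to the worst pairings at the assumed gaps. In the other 8 combinations it is 5.0% to 7.7%.
- **That stratifying by level would gain 9 to 48 points of power.** This assumes zero intracluster correlation, which cannot be relied on with two ASSIRs per arm, and it should not be claimed.

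The objection to a woman-level Mantel-Haenszel estimate as the main test also stands: it would remove the level shift but still ignore clustering by ASSIR. The core is untouched. A factor considered important at allocation is missing from the stated tests, and the quotas allow a material imbalance in the one draw that this trial has.

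**Conclusion.** The point holds as a mismatch between allocation and stated analysis, worth correcting alongside the handling of clustering. With two levels of two ASSIRs split one per arm, the arms can differ in level mix by 1.4 to 30.2 points. For assumed gaps of 10 to 30 points in presentation, the crude difference moves by about 0.1 to 9 points, up or down, against a planned 20. Whether the actual shift is near the top or negligible depends on the hospitals' levels, the draw and the true gap, none of which the Protocol gives. The document does not show that a shift of any particular size will occur.

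**What to change.** In the Analysis section:

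1. State the hospital-level grouping used in the assignment and which ASSIRs fall in each level.
2. Make the main comparison of presentation an ASSIR-level contrast: take the difference between ASSIR proportions within each level, average over levels with equal weights, and use the unpaired between-ASSIR standard error with 2 df. Do the same for satisfaction (means) and sufficiency of information (proportions). One analysis then respects the allocation and carries the clustering.
3. Name hospital level as a covariate in the planned multivariate model, where each level has ASSIRs in both arms.
4. Report the crude chi-square and t tests as supportive only.

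The cost is a few sentences. The level is known for every ASSIR, so no new data or women are needed. Equal weighting loses a little precision (1% to 5% on the standard error, ignoring clustering). The unpaired standard error is conservative because any level gap stays in it; removing the gap instead leaves 1 df and a critical t of 12.7 rather than 4.3. The sponsor should expect a wide interval either way: a half-width of about 28 points before any clustering or level gap already exceeds the planned 20. That width comes from having four clusters, and the pooled tests hide it.

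### Four ASSIRs are randomised, two per arm, but the only hypothesis tests named treat women as independent, so between-arm p-values and confidence intervals are too optimistic

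*Protocol*

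**What the plan says.** The Protocol describes a cluster randomised trial (Abstract; Methodology, Design). Under Subjects, Sampling technique, the allocation is: "Thus, two ASSIRs will be assigned to the intervention group and two to the control". Under Subjects, Sample size, the calculation is "based on the main variable of the study “presentation of birth plans" and is presented as "taking into account the influence of the clusters in the analysis, a total of 133 are required in the control group", with the same number in the intervention group. The inputs are 48% versus 68%, alpha 5%, beta 20% and 15% loss. No ICC or design effect is given, and the text does not say whether 133 already includes the loss.

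The Analysis section, after the homogeneity checks on baseline variables, says: "Hypothesis contrast tests, Chi-square test and Student's t test will be performed". It sets a 5% significance level and adds: "A multivariate analysis, relative risks and number of subjects will be calculated with a confidence interval of 95"%. It names no cluster-level summary, random effect, robust variance or small-sample correction.

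**The concern.** The chi-square and Student's t tests take each woman as an independent observation, whereas the unit assigned to an arm is the ASSIR. Women in one ASSIR share midwives and a reference hospital. The Protocol says that these hospitals differ in level of care, and (Data collection and tools) that the birth-plan form is agreed with each hospital according to its characteristics. Presenting the plan to the hospital plausibly depends on all of this, so some correlation within ASSIR is expected. The sample-size text expects it too.

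The part of the ASSIR variation that lies between the two arms adds to the variance of the treatment contrast, and the named tests leave it out. With only two ASSIRs per arm, ordinary centre differences could then appear as an effect of counselling on presentation, preferences, information or MacKey scores.

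**Working it through.** **Inputs from the Protocol.** 48% and 68%; alpha 5% (two-sided assumed, as sidedness is not stated); power 80%; loss 15%; 133 per arm. Table 1 cluster sizes are 41, 79, 94 and 52, mean 266/4 = 66.5. After 15% loss they are about 35, 67, 80 and 44, mean 66.5 × 0.85 = 56.5.

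**Step 1: what 133 implies.** With individual randomisation, pooled variance and no continuity correction:

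n = [1.96√(2 × 0.58 × 0.42) + 0.842√(0.48 × 0.52 + 0.68 × 0.32)]² / 0.20² = 94.4, so 95 per arm, or 95/0.85 = 112 after loss.

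Neither figure is 133; the gap is the cluster allowance. The implied design effect (DE) is:
- if 133 includes the loss: 133 × 0.85 / 95 = 1.19
- if it does not: 133 / 95 = 1.40

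From DE = 1 + (m − 1) × ICC with m = 66.5, the implied ICC is 0.19/65.5 = 0.003 or 0.40/65.5 = 0.006. With a continuity correction (105 per arm) the design effects are 1.08 and 1.27, and the ICCs about 0.001 and 0.004. So 133 fits a small allowance, but the figure cannot be confirmed because no ICC is stated.

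**Step 2: true size of the nominal 5% test.** Size = 2 × [1 − Φ(1.96/√DE)].
- DE 1.19: 1.96/1.091 = 1.797, size 7.2%
- DE 1.40: 1.96/1.183 = 1.656, size 9.8%
- With the continuity-corrected DEs of 1.08 and 1.27: 5.9% and 8.2%

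**Step 3: a wider range of ICC (assumed, not from the Protocol).**

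| ICC | DE, m = 56.5 | Size | DE, m = 66.5 | Size |
|---|---|---|---|---|
| 0.01 | 1.56 | 11.6% | 1.66 | 12.8% |
| 0.02 | 2.11 | 17.7% | 2.31 | 19.7% |
| 0.05 | 3.78 | 31.3% | 4.28 | 34.3% |

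Beta-binomial simulation of the chi-square test with clusters of 35, 67, 80 and 44, over the three ways of pairing ASSIRs into arms, gives about 7 to 8% at ICC 0.0036 (DE 1.2), 11 to 13% at 0.01, 17 to 20% at 0.02 and 30 to 34% at 0.05. With the full Table 1 sizes it gives 13.6%, 20.8% and 36% at the last three ICCs. A t test on the four ASSIR proportions stays at about 5% throughout.

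**Step 4: what a valid test costs.** An unpaired comparison of four summaries has 4 − 2 = 2 degrees of freedom, so the critical value is 4.30 instead of 1.96. With 113 evaluable women per arm, the unadjusted 95% half-width for the risk difference is 1.96 × √(0.4672/113) = 0.126, where 0.4672 = 0.48 × 0.52 + 0.68 × 0.32. On 2 degrees of freedom at ICC 0.01 (DE 1.555) it is 4.30 × √(1.555 × 0.4672/113) = 0.345. Simulated power for 48% versus 68% is about 34% at ICC 0.0036, 29% at 0.01 and 17% at 0.05.

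**The case against.** The best defence is that the Protocol does not firmly tie chi-square and t to the main comparison. The sentence follows the baseline homogeneity checks, the multivariate analysis is unnamed, and the sample-size text speaks of taking clusters into account in the analysis. A separate analysis plan could specify a cluster-adjusted model. This stands to the extent that a reader should not infer that every comparison is certain to be analysed by woman. It does not remove the point. The phrase about clusters describes how 133 was obtained and names no method, and enlarging a sample does not correct a test. These two tests are the only ones named. Entering ASSIR as a fixed effect in the multivariate model would not help, because arm is fully determined by ASSIR.

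Two further readings go beyond the documents. One is that all variation between ASSIRs is counted as treatment effect. Only the part that falls between the arms enters the contrast; the difference between two ASSIRs of the same arm does not. The other is that false positives will occur about a third of the time. That needs an ICC near 0.05, which the Protocol nowhere supports; its own sample size implies about 0.001 to 0.006. If the ICC were zero there would be essentially no inflation, but the Protocol does not assume zero.

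**Conclusion.** The mismatch is real and must be corrected. The design randomises ASSIRs, the sample size presumes clustering, and the named tests ignore it. The figure anchored in the document is a true type I error of about 7 to 10% in place of 5%, at a design effect of 1.2 to 1.4. It assumes a two-sided test without continuity correction; with the correction it is about 6 to 8%. The larger figures in Step 3 are conditional on assumed ICCs and should be quoted only as such. The direction, p-values too small and intervals too narrow, holds for any positive ICC.

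It is tempting to treat this as a change of wording alone. The Protocol's own numbers do not allow that: once the analysis respects four clusters, the stated beta of 20% no longer holds.

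**What to change.** In the Analysis section, replace the chi-square and t tests for between-arm comparisons of presentation, preferences, information and MacKey scores. Use a cluster-level analysis of the four ASSIR summaries, optionally after a first-stage regression on prespecified baseline covariates that omits arm. Report the t test and 95% intervals on 2 degrees of freedom.

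State how hospital characteristics entered the assignment of ASSIRs, and match the analysis to it. If ASSIRs were paired, a paired comparison of two differences leaves only 2 − 1 = 1 degree of freedom, and this should be faced openly.

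Do not offer a mixed model or GEE as equivalent. With four clusters robust variances are unreliable. The between-ASSIR variance is also often estimated as zero (a moment estimator gave zero or less in about 56% of simulated trials at ICC 0.0036 and 48% at 0.01), which can return the analysis to the level of the woman. Kenward-Roger is a correction for linear models, while the main variable is binary. Comparisons of women within an arm are clustered too, so chi-square and t should not simply be kept there.

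The cost is more than wording. Intervals widen considerably: at ICC 0.01 the half-width goes from about 13 to about 35 percentage points. The sample-size section must state the assumed ICC, say whether 133 includes the 15% loss, and restate power on 2 degrees of freedom. The sponsor should then either randomise more units or acknowledge that four clusters leave the trial underpowered for 48% versus 68%.
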